### Participants

2.3

Participants aged over 65 years will be recruited through different older people’s associations (i.e., La Nau Gran and Asociación Grupo de Mayores de Telefónica). The study will also be advertised on the research group website and social media. The researchers will establish compliance with the selection eligibility criteria described in Table 1. Researchers may terminate a participant’s involvement in the study if changes in the participant’s clinical status result in non-compliance with the established eligibility criteria.

**TABLE 1 T1:** Eligibility criteria.

Eligibility Criteria	
**Inclusion criteria**	**1. Exclusion criteria**
Aged over 65 years	History of stroke within the past 6 months or hospital admission for any reason within the past 3 months
Being prefrail according to Fried criteria	Diseases of the central or peripheral nervous system
Ability to understand instructions (Mini-Mental State Examination > 23 points)	Vestibular system
Signing the written informed consent.	Concomitant diseases Have a neurological pathology, cardiovascular musculoskeletal that contraindicates physical activity Epilepsy or history, medications that lower the seizure threshold Cardiac pacemaker, endocranial and hearing implants History of severe headaches Uncontrolled intracranial or arterial hypertension Heart and/or respiratory failure Implanted medication pump Skin lesions (psoriasis, eczema) Serious head surgeries Completing less than 80% of training sessions

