**Methods and analysis:**

This four-arm, triple-blinded randomized controlled trial will include adults aged ≥ 65 years classified as prefrail according to Fried criteria. Participants will be randomly assigned to one of the following groups: VR+TPE, sham VR+TPE, tDCS+TPE or, sham tDCS+TPE. All interventions will be applied during an 8 week-programme consisting of 24 supervised sessions. The primary outcomes will be frailty status (Fried Phenotype) and walking speed. Secondary outcomes will include neuroplasticity biomarkers (plasma BDNF), heart rate variability, upper and lower limb isometric strength, quality of life (EQ 5D 5L), lower-limb muscle power, static and dynamic functionality, gait quality and dual-task performance. Assessments will be conducted at baseline, immediately after the first session, at 4 weeks, at the end of the 8 week intervention, and at 4 week follow up.

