### Intervention and comparator

2.4

All the interventions will be administered for 24 sessions, 3 days a week, by professional physiotherapists (i.e., more than 5 years of experience). During the intervention, participants will continue their usual pharmacotherapy (which will be registered for subsequent analysis), but other simultaneous physiotherapy treatments will be forbidden. Potential adverse effects arising during the intervention phase or during the follow-up period will be systematically monitored and recorded by the research team. Should an adverse event require clinical attention, the lead investigator will coordinate and guarantee the implementation of the necessary therapeutic measures.

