##### Frailty condition

2.5.1.1

Frailty status will be assessed using the Fried Frailty Phenotype. Participants will be classified as frail if they meet three or more of the following criteria: (i) unintentional weight loss greater than 4.5 kg in the previous year; (ii) self-reported exhaustion; (iii) low level of physical activity; (iv) slowness, determined by gait speed; and (v) muscle weakness, assessed by handgrip strength. Participants meeting one or two criteria will be classified as pre-frail, whereas those meeting none of the criteria will be considered robust. The Fried Frailty Phenotype has demonstrated good predictive validity and reliability for adverse health outcomes in older adults (Fried et al., 2001).

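### Table 1 makes attendance below 80% of sessions an exclusion criterion, which excludes participants after randomisation on something the interventions can affect

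*Protocol article*

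**What the plan says.** Table 1 in section 2.3 (Participants) gives the eligibility criteria. The last entry in the exclusion column is "Completing less than 80% of training sessions". Section 2.4 fixes the denominator: "All the interventions will be administered for 24 sessions, 3 days a week". Under section 2.6, the sealed envelope with the allocation is opened once the participant has been formally enrolled.

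Section 2.3 also contains a discretionary rule: "Researchers may terminate a participant’s involvement in the study if changes in the participant’s clinical status result in non-compliance with the established eligibility criteria". One of the inclusion criteria in Table 1 is "Being prefrail according to Fried criteria". The abstract states: "The primary outcomes will be frailty status (Fried Phenotype) and walking speed". Section 2.5.1.1 defines the categories: "Participants meeting one or two criteria will be classified as pre-frail, whereas those meeting none of the criteria will be considered robust". Three or more criteria count as frail.

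Section 2.7 allows for 20% losses in every group. Section 2.9 plans a mixed-design ANOVA over five assessments, with two groups per sub-study. The Discussion says that adherence and attrition will be recorded, and gives feasibility as the purpose.

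**The concern.** An eligibility criterion should be decidable before allocation. Nobody has attended a session at that point, so the attendance line can act only on people who already have an assigned arm. It therefore selects participants by an event that follows treatment and that treatment may influence.

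The protocol gives its own reasons to doubt that poor attenders are a random subset. The Introduction says that physical limitation and fatigue from exercise can make it hard for frail and prefrail people to keep to the prescription. The Discussion presents neuromodulation as a way to add benefit without the fatigue that lowers adherence. On that rationale, attendance may depend both on prognosis and on arm. Those are the two conditions under which a post-randomisation exclusion biases the comparison.

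The secondary point concerns the termination rule. Everyone enters prefrail, so a later change of category, in either direction, is also a departure from an inclusion criterion. The rule does not say that the prefrail criterion is exempt.

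**Working it through.** **Threshold.** 0.80 × 24 = 19.2 sessions. Attending 19 (19/24 = 79.2%) triggers the exclusion; attending 20 (20/24 = 83.3%) does not. Missing five sessions in eight weeks is enough.

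**The plan's loss allowance.** 16 / (1 − 0.20) = 20 per group, and 4 × 20 = 80 in total. The inflation step reproduces. It allows for up to 0.20 × 80 = 16 losses from all causes. The document does not say how many would come from the attendance rule.

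**Shift in one arm.** Let p be the share removed, K the mean of those kept and R the mean of those removed. The full-arm mean is (1 − p)K + pR, so the mean after removal exceeds it by p(K − R). The bias in the between-arm difference is p₁(K₁ − R₁) − p₂(K₂ − R₂).

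Assumed illustration: p₁ = 0.20, K₁ − R₁ = 0.20 m/s, and nobody removed from the other arm.

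- Shift = 0.20 × 0.20 = 0.04 m/s.
- Relative to the target in section 2.7: 0.04 / 0.19 = 21%.
- If the other arm has the same p and the same K − R, the two terms cancel and the bias is zero.

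**How it depends on the assumptions.** A simulation used 20 per arm, SD 0.29 m/s (section 2.7), no true difference, a two-sided t-test at 5% on one outcome, and 6,000 runs per case. Attendance was given an assumed correlation with outcome, and the poorest attenders were removed. Every row averages 20% removed over the two arms. Cells show bias in m/s and type I error.

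| Removed, arm 1 v arm 2 | Correlation 0.3 | 0.5 | 0.7 |
|---|---|---|---|
| 20% v 20% | 0.00; about 5% | 0.00; about 5% | 0.00; about 5% |
| 25% v 15% | 0.01; 4.7% | 0.02; 5.6% | 0.03; 6.0% |
| 30% v 10% | 0.03; 5.2% | 0.04; 6.8% | 0.06; 9.1% |
| 40% v 0% | 0.06; 7.8% | 0.09; 13.1% | 0.13; 23.7% |

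At zero correlation, no pattern of removal produced bias. Simulation error on a 5% rate is √(0.05 × 0.95 / 6,000), about 0.3 percentage points, so the smallest departures from 5% are not distinguishable from none. The removal rates and correlations are assumptions; the document gives neither.

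**The termination rule, by comparison of sections.** Section 2.3 ties termination to a change in clinical status that breaks eligibility. Table 1 makes prefrail status part of eligibility. Section 2.5.1.1 treats robust and frail as outcome categories. Section 2.1 schedules assessments through T5, four weeks after the intervention ends. Read literally, the first two would let a researcher end someone's involvement because of a primary outcome. The last two show that the trial intends to observe that change.

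**The case against.** Four things can be said for the plan.

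First, section 2.3 does not say what exclusion means in practice: ending sessions, ending assessments, or leaving data out of the analysis. Analysis sets are commonly defined in a full protocol or SAP, and neither is shown. This stands as a limit. A reader might infer that the trial will certainly be analysed on attenders only, so that the randomised comparison is lost. The document does not go that far, and the lack of an intention-to-treat sentence in section 2.9 is no evidence either way. The point rests on the line that Table 1 does contain, which nothing in the document confines to a per-protocol set.

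Second, all arms share the treadmill walking and the exercise programme, and each technique has its own sham. Attendance may well be similar across arms, in which case the bias is small. This also stands, and it is why no size is claimed. It does not make the rule sound, because similar attendance cannot be known in advance.

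Third, the extracted layout of Table 1 is broken. The attendance wording itself is intact and sits in the exclusion column.

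Fourth, a reader might infer that section 2.3 removes everyone who becomes robust or frail, deleting the events that the primary outcome counts. The documents do not support that reading. The rule says researchers may terminate, it is tied to clinical status, and most of the Table 1 exclusions are conditions that could make exercise or stimulation unsuitable. Categories other than prefrail are planned results. The rule was probably meant for safety conditions. What remains is that its wording does not exempt prefrail status.

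**Conclusion.** The attendance line is a stated post-randomisation exclusion placed among entry criteria, and it should be corrected. That much follows from Table 1 and section 2.6 without any assumption.

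The effect on the results cannot be quantified from the document. It is about zero if exclusion acts alike in the two arms being compared, or is unrelated to outcome. It is 0.04 m/s, about a fifth of the target difference, under the assumed one-arm case above. It can be larger if removal is strongly unequal and closely tied to outcome. No size is offered for the frailty outcome.

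The termination rule is a lesser matter: an ambiguity that calls for one clarifying clause.

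**What to change.** - Delete the attendance line from the eligibility criteria in Table 1.
- State that all randomised participants are invited to every scheduled assessment through T5, subject to their right to withdraw (section 4), and are analysed in their allocated group whatever their attendance.
- Report the participants who attended at least 80% of sessions only as a sensitivity (per-protocol) analysis.
- Add one clause to section 2.3: the prefrail criterion applies at entry only, so a later change of frailty category is an outcome and not a reason to end outcome assessment or remove data.
- Keep decisions about continuing sessions separate from outcome assessment. This point takes no position on those decisions.

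The cost is protocol wording, plus invitations to visits that are already scheduled. The downside is that the main estimate will include poor attenders and may be slightly diluted; the sensitivity analysis shows the result among those who attended.

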### Intervention and comparator

2.4

All the interventions will be administered for 24 sessions, 3 days a week, by professional physiotherapists (i.e., more than 5 years of experience). During the intervention, participants will continue their usual pharmacotherapy (which will be registered for subsequent analysis), but other simultaneous physiotherapy treatments will be forbidden. Potential adverse effects arising during the intervention phase or during the follow-up period will be systematically monitored and recorded by the research team. Should an adverse event require clinical attention, the lead investigator will coordinate and guarantee the implementation of the necessary therapeutic measures.

#### Experimental intervention 1: VR + TPE

2.4.1

The participant will be instructed to walk at a somewhat-hard to hard-pace (i.e., 4–5 on the Borg Scale of rated perceived effort (RPE)) on a treadmill, with a mirror located just in front of him at waist height. He will be asked to watch at a height-adjustable screen (from waist to caudal) where a video of real legs running on a treadmill will be projected for 20 min. To ensure that the participant feels the projected legs as their own, projected legs will be adapted to each subject according to their height and weight. After 20 min of VR + walking, the participant will undergo a multicomponent TPE training for 40 min, including strength, balance, coordination and mobility. The Borg Scale was administered during each session to assess participants’ perceived exertion, including effort, fatigue and breathlessness experienced throughout the intervention in order to monitor and control session-related fatigue and ensure that exertion did not exceed the prescribed threshold. When participants reported an exertion level below “moderate” on the scale, the intensity was progressively increased by introducing greater external loads and/or incorporating unstable surfaces to enhance the overall physical demand. This instrument has demonstrated high reliability (Intraclass Correlation Coefficient, ICC = 0.88 to 0.93) (Mendelsohn et al., 2008).

#### Placebo Comparator 1: sham VR + TPE

2.4.2

The intervention will be the same as the former group, yet the video projection will consist of landscapes without featuring any type of human or animal movement, in order not to stimulate the motor areas of the brain.

#### Experimental intervention 2: tDCS + TPE

2.4.3

Anodal tDCS (a-tDCS), will be administered, using a battery-driven direct current stimulator (EPTE^®^ Bipolar System, Ionclinics, Spain). Two saline-soaked sponge electrodes (35 cm^2^) will be secured in place by a neoprene helmet, in accordance with the EEG 10–20 International System, for optimal targeting of the primary motor cortex M1. The anodal electrode will be located on the primary motor cortex (M1), while the cathode will be positioned over the contralateral supraorbital cortex. The treatment parameters will be: stimulation time of 20 min; intensity of 2 mA, current rise-fall time at the beginning and end of stimulation of 30 s. The 20-minute tDCS session will be administered concurrently with treadmill walking. Following the stimulation period, participants will proceed to perform the TPE protocol described above.

#### Placebo Comparator 2: sham tDCS + TPE

2.4.4

The instrumentation and setting will be the same as in the real tDCS intervention (i.e., tDCS while walking on a treadmill), but the device will be programmed to increase the intensity from 0 to 2 mA progressively during the first 30 s and then cease with a 30-seconds ramp-down, thus providing the participant with the initial itchy sensation on the skin, similar to the real application. In prior studies, this approach has been shown to ensure participant blinding regarding the stimulation type (active vs. sham) (Antal et al., 2017). They will then perform the TPE protocol explained above.

### Outcomes

2.5

#### Primary outcome measures

2.5.1

##### Frailty condition

2.5.1.1

Frailty status will be assessed using the Fried Frailty Phenotype. Participants will be classified as frail if they meet three or more of the following criteria: (i) unintentional weight loss greater than 4.5 kg in the previous year; (ii) self-reported exhaustion; (iii) low level of physical activity; (iv) slowness, determined by gait speed; and (v) muscle weakness, assessed by handgrip strength. Participants meeting one or two criteria will be classified as pre-frail, whereas those meeting none of the criteria will be considered robust. The Fried Frailty Phenotype has demonstrated good predictive validity and reliability for adverse health outcomes in older adults (Fried et al., 2001).

##### Walking speed

2.5.1.2

The 10-Meter Walk Test will be used to assess walking speed. The participant will be instructed to walk as fast as possible over a total distance of 14 meters, including 2-meter acceleration and 2-meter deceleration phases. Maximum walking speed will be recorded over the intermediate 10-meter distance. The average of three trials (1-minute rest between them) will be calculated for subsequent analysis. The test has demonstrated excellent reliability, with ICC values ranging from 0.89 to 0.99 (Perera et al., 2006).

#### Secondary outcome measures

2.5.2

##### Neuroplasticity biomarkers

2.5.2.1

Neuroplasticity biomarkers will be determined by assessing plasma BDNF levels. A nurse will draw blood samples in BD Vacutainer^®^ tubes, with EDTA as an anticoagulant. After being centrifuged at 1500 *g* for 15 min at 4°C, the supernatant (total plasma) will be centrifuged again at 10,000 *g* for 10 min at 4 °C to remove platelets (Rasmussen et al., 2009); then, the resulting supernatant (platelet-free plasma) will be collected in Eppendorf-type tubes, which will be frozen at −80°C until subsequent analysis. For the determination of plasma BDNF levels, the ChemiKine™ BDNF Sandwich kit for ELISA (Millipore, Temecula, CA, USA) will be used according to the manufacturer’s instructions.

##### Heart rate variability

2.5.2.2

Heart rate variability (HRV) will be continuously recorded using a chest strap device (Polar H10; Polar Electro Oy, Kempele; Finland) at three different time points: (i) 5 min at rest while lying in a supine position at the beginning of each assessment session; (ii) during the 6 mWT to evaluate the effect of the intervention in HRV in the exertional test at each of the time assessment points; (iii) during the first 20 min of the first session of each experimental intervention (i.e., VR/tDCS + walking) to explore acute effects of each intervention. Time-domain HRV indices will include mean RR interval duration (RRi), the standard deviation of normal-to-normal intervals (SDNN), the root mean square of successive differences between adjacent normal RR intervals (rMSSD), and the proportion of consecutive RR intervals differing by more than 50 ms (pNN50). Frequency-domain parameters will encompass low-frequency power (LF; 0.04–0.15 Hz), high-frequency power (HF; 0.15–0.40 Hz), the LF/HF ratio, and total power (TP). For statistical analysis, only the final segment of the recording will be considered, with the initial 2 min excluded to account for the stabilization phase (Pereira et al., 2016).

Data will be exported as.txt files from the Elite HRV application (Elite HRV LLC, USA) and subsequently analyzed using Kubios HRV version 3.5 (Kubios Oy, Finland). The recordings will be carefully reviewed to detect artifacts and ectopic beats (less than 3%), which will be manually corrected and substituted through interpolation based on adjacent RR intervals (Pereira et al., 2016).

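### The 2-minute stabilisation period is taken out of the 5-minute supine HRV recording, so at most 3 minutes are analysed and the resting indices are less precise than they need be

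*Protocol article*

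**What the plan says.** The abstract of the protocol article places HRV among the secondary outcomes: "Secondary outcomes will include neuroplasticity biomarkers (plasma BDNF), heart rate variability". Section 2.5.2.2 sets three recordings:

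- at rest: "5 min at rest while lying in a supine position at the beginning of each assessment session";
- in the exertional test: "during the 6 mWT to evaluate the effect of the intervention in HRV in the exertional test";
- in the intervention itself: "during the first 20 min of the first session of each experimental intervention".

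It lists mean RR interval, SDNN, rMSSD and pNN50, then "low-frequency power (LF; 0.04–0.15 Hz" as the lower band edge and range for LF, and "high-frequency power (HF; 0.15–0.40 Hz), the LF/HF ratio, and total power (TP" for the rest of the spectrum. No index is tied to a particular recording.

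One rule then governs what is analysed: "only the final segment of the recording will be considered, with the initial 2 min excluded to account for the stabilization phase". The rule cites a source and exempts no recording. It does not say how long the final segment is. Section 2.9 compares two groups over the five assessments and mentions no comparison of HRV values between recording types.

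**The concern.** The settling period is cut from inside the 5 min of rest instead of coming before it. That discards 2/5 = 40% of the resting record. The indices most affected are those that depend on slow oscillations: LF, the LF/HF ratio, SDNN and total power. A shorter window holds fewer slow cycles, so each estimate is noisier, and this recurs at every assessment in two-group sub-studies with 20 participants planned per arm (section 2.7).

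A second, conditional matter follows from the same rule. Applied to recordings of different length, it can leave windows of very different length. SDNN and total power grow with window length when slow components are present, so values from different recordings would not be the same quantity.

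**Working it through.** **Inputs from section 2.5.2.2.** Supine recording 5 min; first-session recording 20 min; initial exclusion 2 min; LF band 0.04–0.15 Hz, width 0.11 Hz. **Assumption.** The walk test lasts 6 min, read from its name, since no duration is given. The article states no analysed window length, so there is no figure of its own to reproduce.

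**1. Longest possible analysed window = recording − 2 min.**
- Supine: 5 − 2 = 3 min (180 s)
- Walk test: 6 − 2 = 4 min
- First session: 20 − 2 = 18 min
- Largest ratio: 18/3 = 6, if everything after minute 2 is used

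**2. Cycles at the slowest LF frequency = window × 0.04 Hz.**
- 180 s × 0.04 = 7.2
- 300 s × 0.04 = 12

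**3. Is LF still computable?** Frequency resolution at 180 s is 1/180 = 0.0056 Hz. The LF band then holds 0.11 × 180 = 19.8, about 20, frequency bins, against 0.11 × 300 = 33 at 300 s. So it can be computed, with fewer bins to average.

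**4. Precision of one LF estimate.** Two separate simulations with assumed spectra were run. Simulation A used 1,500 series with a 1/f spectrum up to 0.4 Hz. Simulation B used series with flat LF and HF bands, with and without a 1/f component below 0.04 Hz (linear detrending, Hann periodogram).

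| Assumed spectrum | LF CV, 3 min | LF CV, 5 min | Variance ratio |
|---|---|---|---|
| A: 1/f to 0.4 Hz | 0.338 | 0.253 | (0.338/0.253)² = 1.79 |
| B: no slow component | 0.317 | 0.250 | (0.317/0.250)² = 1.61 |
| B: 1/f below 0.04 Hz | 0.307 | 0.248 | (0.307/0.248)² = 1.53 |

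If estimation variance falls as 1/length, a ratio of 5/3 = 1.67 is expected, which lies inside this range. In simulation B the mean values at 3 min were 0.97–1.00 (SDNN), 0.94–0.97 (LF) and 0.92–1.00 (total power) of the 5-min values, so the shift in level is small.

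**5. Window length alone, 18 min against 3 min, with no physiological change.**

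| Assumed spectrum | Total power | SDNN |
|---|---|---|
| A: 1/f to 0.4 Hz | 1.230/0.917 = 1.34 | 1.112/0.956 = 1.16 |
| B: 1/f below 0.04 Hz | 1.159/0.924 = 1.25 | 1.053/0.971 = 1.08 |
| B: no slow component | 1.010/0.998 = 1.01 | 1.002/0.999 = 1.00 |

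The range is from under 5% to about 34% for total power, and from under 5% to about 16% for SDNN.

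**The case against.** A reader might infer that 3 min is too short for these indices to be valid. The documents do not support that. They give no minimum length, and LF remains computable from about 20 bins. The answer also turns on the criterion chosen: an assumed requirement of 5 cycles at 0.04 Hz needs 5/0.04 = 125 s, which 180 s meets, while 10 cycles needs 250 s, which it does not. The exclusion rule also cites a source that is not at hand.

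A reader might also infer that windows differing up to six-fold distort the trial's HRV results. They would do so only if values were compared between recording types. Section 2.9 plans no such comparison, and section 2.5.2.2 gives each recording its own purpose. Within one recording type both groups and all visits follow the same rule, so the randomised contrast carries no bias from window length. An acute comparison with equal windows is also available from the supine recordings at T1 and T2. Six-fold is itself an upper bound, because the length of the final segment is not stated, and a condensed article may leave that to the full protocol.

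Finally, estimation noise is only part of the total variance. As an illustration, assume all other variation in LF has a CV of 50% to 100%. Raising the estimation CV from 25% to 34% then moves the total from √(0.50² + 0.25²) = 0.56 to √(0.50² + 0.34²) = 0.60, or from √(1.00² + 0.25²) = 1.03 to √(1.00² + 0.34²) = 1.06. That is an increase of about 8% or 2%.

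All of this stands, and it limits the point. It does not remove the fact that the stated rule discards two of the five resting minutes, and that this loss is avoidable.

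**Conclusion.** The point holds as an avoidable loss of precision in a secondary outcome. At most 3 min of supine data are analysed, which follows directly from two figures in section 2.5.2.2. Under the assumed spectra, the LF estimation CV is about 31–34% where a full 5-min window would give 25%. The effect on the total variance is smaller and depends on between-person variation that the article does not give.

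The documents do not show that the indices are invalid or that any planned group-by-time contrast is biased. The unequal windows matter only if session or walk-test values are set against rest; the size in that case depends on the spectrum and could be negligible. Neither primary outcome is touched. Severity is minor.

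**What to change.** - Record 7 min supine at each assessment: 2 min of stabilisation, then 5 min analysed. This restores 12 cycles at 0.04 Hz.
- State one fixed analysed window length for each recording type.
- Add that SDNN and total power will be compared between rest, walk test and first session only over a common window length.

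The cost is two more minutes lying down per visit, or 2 × 5 = 10 min per participant if all five assessments include the supine recording, plus a sentence or two of text. No extra staff or equipment is needed.
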